## Abstract

**Background:**

Adjustment Disorder (AjD) is a common and disabling mental health problem. The lack of research on this disorder has led to the absence of evidence-based interventions for its treatment. Moreover, because the available data indicate that a high percentage of people with mental illness are not treated, it is necessary to develop new ways to provide psychological assistance. The present study describes a Randomized Controlled Trial (RCT) aimed at assessing the effectiveness and acceptance of a linear internet-delivered cognitive-behavioral therapy (ICBT) intervention for AjD.

**Methods:**

A two-armed RCT was designed to compare an intervention group to a waiting list control group. Participants from the intervention group will receive TAO, an internet-based program for AjD composed of seven modules. TAO combines CBT and Positive Psychology strategies in order to provide patients with complete support, reducing their clinical symptoms and enhancing their capacity to overcome everyday adversity. Participants will also receive short weekly telephone support. Participants in the control group will be assessed before and after a seven-week waiting period, and then they will be offered the same intervention. Participants will be randomly assigned to one of the 2 groups. Measurements will be taken at five different moments: baseline, post-intervention, and three follow-up periods (3-, 6- and 12-month). BDI-II and BAI will be used as primary outcome measures. Secondary outcomes will be symptoms of AjD, posttraumatic growth, positive and negative affect, and quality of life.

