### Randomization and blinding

Participants included in the study will have to sign the participation agreement without having a priori knowledge about their group assignment. Study researchers will also be blind to the group to which the assessed participants will belong. Once the online informed consent has been signed, an independent researcher will perform a “blocked randomization”, guaranteeing that the same number of participants are allocated to each condition (ICBT or WL). This allocation will be performed following a random number sequence generated by the Epidat 4.1 program.

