### Sample size

The sample size for the trial was calculated following the method described by Campbell, Julious, and Altman [37], and Freiman, Chalmers, Smith, and Kuebler [38]. G*Power 3 software [39] was used to facilitate power analysis.

Because there is no published research on the effectiveness of ICBT for the treatment of AjD, the sample size was calculated taking into account outcomes found in trials that used the BAI and BDI-II as measures of clinical change after an ICBT intervention in patients with clinical depression or anxiety disorder [40–42]. After reviewing the literature and adopting a more conservative approach, an effect size of .70 was assumed in the present study. Considering a significance level of 5% and a power of 80%, 26 participants in each group would be enough to detect the assumed difference. However, because the literature reveals dropout rates from ICBTs of around 30% [43], a sample of 68 participants will be recruited (34 per group).

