#### Primary outcome measures

*Beck Depression Inventory - Second Edition (BDI-II)* [50]*,* validated in the Spanish population [51]. The BDI-II is a widely used self-report inventory that measures characteristic attitudes and symptoms of depression. The total score is obtained by adding the scores on the 21 items that make up the instrument, with a maximum of 63 points. The instrument has good internal consistency (Cronbach’s alpha of 0.76 to 0.95) and test-retest reliability of around 0.8.

*Beck Anxiety Inventory (BAI)* [52], validated in the Spanish population [53]. The BAI measures the severity of both physiological and cognitive symptoms of anxiety. The 21 items are rated on a 4-point Likert-type scale (from 0 to 3), and the total score, which ranges between 0 and 63, is obtained after directly adding together the scores on all the items. Psychometric analyses carried out so far show excellent internal consistency (Cronbach’s alpha ≥0.85).

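### Two primary outcomes share one 5% level and a sample size for one comparison, and the protocol does not say whether one or both must be significant

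*Protocol article*

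**What the plan says.** The Methods part of the abstract states that "BDI-II and BAI will be used as primary outcome measures", and the section on primary outcome measures lists both scales without ranking them.

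The sample size section gives a single standardized effect for both scales ("an effect size of .70 was assumed in the present study") and a single error level and power: "Considering a significance level of 5% and a power of 80%, 26 participants in each group would be enough to detect the assumed difference". It then raises 26 to 34 per group, 68 in total, for dropout of around 30%. It does not say whether the test is one-sided or two-sided.

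The data analyses section names repeated-measures ANOVAs for primary and secondary outcomes alike. It gives no success rule for the two primary scales, no test order and no division of the significance level. It also says that analytic methods will be reviewed before the data are analysed, but does not say that the review will settle this question.

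**The concern.** The trial is meant to support one claim, that TAO is effective, and has two primary outcomes on which to base it. The error level and power are stated for a single comparison. Once there are two, neither figure describes the claim until a success rule is given:

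- If a significant result on either scale is enough, there are two chances of a false positive, and the error for the claim exceeds that of one test.
- If both scales must be significant, the error is held, but the chance of success is lower than the power for one scale.

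With no rule fixed in advance, the claim could come to rest on whichever scale gave the better result.

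**Working it through.** **Inputs.** From the sample size section: d = 0.70, 5% level, 80% power, 26 per group, 34 per group recruited, dropout about 30%. Allocation is 1:1 (randomization section). The correlation r between the two test statistics is not given, so I take 0 to 0.9 as an assumption. Power is for a two-group t-test unless noted.

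**1. The plan's own figure.** The noncentrality at 26 per group is d × √(n/2) = 0.70 × √13 = 2.524.

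- One-sided 5%: 2.524 − 1.645 = 0.879, power 81.0% by the normal approximation and 80.1% by the t-test. The t-test needs 25.94, so 26. This reproduces the stated figure.
- Two-sided 5%: 2.524 − 1.960 = 0.564, power 71.4% (normal) or 69.7% (t-test). The t-test needs 33.02, so 34.

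The stated 26 therefore fits one test, at one-sided 5%.

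**2. Either scale suffices, 5% each.** For independent tests the family-wise error is 1 − (1 − 0.05)² = 9.75%. For correlated tests it is 1 minus the bivariate normal probability that neither statistic passes its critical value.

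| r | Two-sided, any direction | Two-sided, only results favouring TAO | One-sided 5%, favouring TAO |
|---|---|---|---|
| 0 | 9.75% | 4.9% | 9.75% |
| 0.3 | 9.5% | 4.8% | 9.3% |
| 0.5 | 9.1% | 4.5% | 8.8% |
| 0.7 | 8.4% | 4.2% | 8.0% |
| 0.9 | 7.0% | 3.5% | 6.8% |
| Single test | 5% | 2.5% | 5% |

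Every entry exceeds that of a single test in its own column.

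**3. Both scales must be significant.** The error is at most 5%. Power at 26 per group, with d = 0.70 on each scale:

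- One-sided (normal approximation): 0.810² = 66% at r = 0, 70% at r = 0.5, 76% at r = 0.9.
- Two-sided (t-test): 0.697² = 49% at r = 0, and about 55% at r = 0.5 and 57% at r = 0.6 by simulation. It cannot exceed the 69.7% for one scale.

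All are below 80%.

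**4. Holm's procedure, two-sided, d = 0.70 on both scales.** The smaller p-value is compared with 2.5% and, if that succeeds, the other with 5%.

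- 26 evaluable per group: per-scale power falls from about 70% to about 64%. If only one scale has an effect it is about 59%, essentially the power of one test at 2.5% (58.7%). The chance that at least one scale succeeds is about 75% at r = 0.5 and 73% at r = 0.6.
- 34 evaluable per group, which requires no dropout: per-scale power falls from 81% to about 77%, or to 72% if only one scale has an effect.

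**The case against.** The strongest reply is that this is a condensed article. Multiplicity rules are commonly left to an analysis plan, which is not shown, and the article itself postpones the choice of methods. That would answer a complaint about missing detail alone. It does not answer this one in full, because the success rule determines the sample size, and the article does fix the sample size, for one comparison, while naming two primary outcomes.

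A reader might go further and infer that each scale is to be tested at 5%, that either suffices, and that the chance of a false claim of effectiveness is therefore about 9% instead of a promised 5%. The document does not support that reading:

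- The only 5% is an input to the sample size. It is not called a level per outcome or an overall rate.
- An either-scale rule is nowhere stated. Under a both-scales rule the error is at most 5%.
- With two-sided tests, about 9% includes results favouring the waiting list. The chance of a false claim of benefit is 3.5% to 4.9%, and the fair comparison is 2.5%. A false-benefit rate near 9% needs one-sided 5% tests, which the stated 26 implies but the text does not declare.

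Two more objections stand. Power and cost must be judged at the evaluable number, not at the 34 recruited. And Holm is one acceptable rule among several; requiring both scales, or testing in a fixed order, would also control the error.

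**Conclusion.** The point holds in a conditional form. The protocol has two primary outcomes, one significance level and a size for one comparison, and no rule connecting them, so the error rate and power of the effectiveness claim are not fixed. Under an either-scale rule at 5% each, the error is about 1.4 to 2 times that of a single test (7.0% to 9.75% against 5%, or 3.5% to 4.9% against 2.5% for false benefit with two-sided tests). Under a both-scales rule the error is sound, but the stated 80% does not apply to the claim.

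These figures rest on an assumed correlation of 0 to 0.9, on d = 0.70 for both scales in the power results, and on a simple two-group comparison. With two-sided tests, 26 per group already gives only 70% for a single scale, so the both-scales rule widens that shortfall and is not its only cause. The matter should be settled before analysis; it does not show that a false claim will be made.

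**What to change.** State the success rule, and whether tests are one-sided or two-sided, before any outcome data are seen. One workable wording: TAO will be considered effective if BDI-II or BAI shows a significant between-group difference in its favour under Holm's procedure (two-sided; smaller p-value at 2.5%, then the other at 5%); both estimates will be reported with confidence intervals whatever the result. With no effect on either scale, false claims of benefit are then at most 2 × 1.25% = 2.5%, the level of a single two-sided test. If the sponsor prefers that both scales succeed, or a fixed order, that should be stated instead and the power given for that rule.

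The text costs a sentence or two. The price in power, two-sided at 26 evaluable per group, is the fall from about 70% to about 64% per scale (59% if only one scale responds). If 30% of 34 are lost, 34 × 0.70 = 23.8, about 24, remain per group, and power for one test is 66% at 5% and 55% at 2.5%. Restoring 80% per scale at 2.5% would need 41 evaluable per group two-sided (t-test 40.08) or 34 one-sided (33.02).

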**Discussion:**

The development of ICBT programs like TAO responds to a need for evidence-based interventions that can reach most of the people who need them, reducing the burden and cost of mental disorders. More specifically, TAO targets AjD and will entail a step forward in the treatment of this prevalent but under-researched disorder. Finally, it should be noted that this is the first RCT focusing on an internet-based intervention for AjD in the Spanish population.

**Trial registration:**

ClinicalTrial.gov: NCT02758418. Trial registration date 2 May 2016.

## Background

Adjustment disorder (AjD) refers to the clinical symptomatology that appears in response to an identifiable stressful event, such as separation or divorce, job loss, diagnosis of a disease, or family conflicts. In order for the diagnosis of AjD to be made, symptoms must begin within 3 months after the stressor and disappear within a period of not more than 6 months once the stressor or its consequences have terminated. Because the presence of an identifiable stressor is the key characteristic of this disorder, in the DSM-5 [1] AjD was classified under the new category of trauma and stress-related disorders. The same change has been proposed for the ICD-11, along with the proposal of a new diagnostic concept [2]. Despite these improvements, the category of AjD is not yet sufficiently clear [3] and a recent review study [4] revealed that there is still little support for the ICD-11 proposal of two symptom structure of AjD (preoccupation with a stressor or its consequences and failure to adapt).

According to the different studies carried out so far, AjD is a very common condition [3, 5, 6]. It is estimated to have an incidence of between 5 and 20% in mental health services, and about 50% in psychiatric consultation settings [1]. AjD is also one of the most frequent diagnoses in patients with organic diseases and surgical interventions [7–11], and in cases of absenteeism and work disability [12, 13]. In addition to being a highly prevalent disorder, AjD causes considerable distress and marked impairment in different functional areas of patients’ lives (e.g., family, friendships, school/work, etc.), and it may increase the risk of suicidal thinking and behavior [14, 15].

Despite these worrisome facts, little research has been conducted to identify and develop evidence-based interventions (EBI) for AjD. To the best of our knowledge, no specific EBI are available for AjD, just some suggestions and recommendations [3, 16]. Furthermore, only a few interventions for AjD have been assessed in a randomized controlled trial (RCT) [13, 17, 18]. Cognitive Behavioral Therapy (CBT) predominates in all of them, although other approaches are also included, such as the use of mindfulness.

In any case, the availability of an effective intervention does not guarantee that it reaches everyone who might need it. Internet-delivered cognitive-behavioral therapy (ICBT) might be a feasible solution for this problem. Currently, data on the efficacy of ICBT are available for a wide range of psychological disorders, including stress-related disorders [19–23]. Some of the main advantages of these kinds of interventions are confidentiality, cost savings, flexibility because patients can access the treatment at any time and from anywhere, and the possibility of reaching patients who would otherwise never receive psychological assistance [24, 25].

Three brief computer-based interventions are available for the treatment of AjD symptoms. “iCanADAPT Early” is a transdiagnostic ICBT designed to treat depression and anxiety disorders in cancer settings [26]. Although the program can be used for the treatment of AjD, it was not developed specifically for this condition. Moreover, the inclusion of cancer-specific CBT skills hinders the use of “iCanADAPT Early” with patients who suffer from AjD due to other stressful events. Seren@ctif is a stress management program based on CBT, developed to treat anxiety related to stress [27]. The program focuses only on AjD with an anxiety subtype, and it is not yet accessible via the Internet. Patients have to go to the hospital and access the program on one of the computers available there. Finally, BADI is an online intervention for AjD that includes CBT, mindfulness, and body-mind practices [28]. The program presents a modular format, giving users the possibility of choosing the content they want to work on. Preliminary positive findings were recently published for a BADI intervention [29]. However, the high dropout rates were identified as the primary limitation of the intervention, and they were attributed to its modular and unguided format.

The only self-help intervention for AjD validated to date is a bibliotherapy manual developed by Bachem and Maercker [30] for burglary victims. It is based on cognitive behavioral techniques that have been validated for the treatment of depressive, anxiety, or post-traumatic stress disorders, including behavioral activation, exposure, cognitive restructuring, and relaxation. The manual has been shown to be a feasible and effective solution for AjD symptoms. However, it has not been validated for AjD resulting from other stressors.

Given the impact and prevalence of AjD, we have developed TAO (*Trastornos Adaptativos Online*). TAO is the first online manualized intervention protocol for AjD developed for the Spanish-speaking population. The linear format of the program makes it possible to progressively start to solve the problematic situation. It is based on the CBT intervention protocol developed by Botella, Baños, and Guillén [31], which, to the best of our knowledge, is the first protocol specifically designed for AjD, showing efficacy in several studies [17, 32]. The aim of this study is to present the RCT that will be conducted to examine the effectiveness of TAO in reducing the distress and clinical symptoms of AjD, compared to a waiting list control group. Additionally, the level of patients’ acceptance and satisfaction with the intervention will be assessed.

## Methods/Design

### Study design

The study is designed as a two-armed, single-blind, parallel group RCT. The trial was registered on the ClinicalTrial.gov database as NCT02758418, and it will be conducted following the Consolidated Standards of Reporting Trials (CONSORT) [33], the CONSORT extension for Electronic and mobile Health Applications and onLine TeleHealth interventions (CONSORT-EHELTH) [34], and the SPIRIT guidelines (Standard Protocol Items: Recommendations for Intervention Trials) [35, 36]. All suitable participants for the trial will be randomly allocated to the intervention group (ICBT) or the Waiting List Control Group (WL). The online informed consent form will be signed before the randomization. Outcome measures will be assessed at baseline, post-intervention, and 3-, 6-, and 12-month follow-ups, in order to provide data on intervention effectiveness and maintenance of the improvements achieved. Fig. 1 displays the flow chart of the study design.

**Fig. 1 Fig1:**
[figure not shown]
Flowchart of participants

### Recruitment

The trial will be announced on local media (radio, TV, newspaper…) and the website of Universitat Jaume I, and disseminated through social networks (i.e., Facebook and Twitter). The advertisement will be published in newspapers, and information brochures will be placed on noticeboards at local universities (Universitat Jaume I and Universitat de València) and nearby towns.

People interested in the study will be encouraged to send an e-mail to [contact]. The clinical team involved in the study will respond to all e-mails within 24 h and arrange a telephone interview. The interview will last about 40–60 min, and its purpose will be to explain the terms of the clinical trial and check the fulfillment of eligibility criteria. The diagnostic interview will be administered to potential participants during this telephone call.

### Eligibility criteria

In order to be included in the trial, participants must meet the following inclusion criteria: (1) be 18 years old or more; (2) meet DSM-5 [1] criteria for AjD; (3) be able to understand and read Spanish; (4) be able to use a computer and have access to the Internet; (5) have an e-mail address. On the other hand, assessed participants who meet any of the following criteria will be excluded from the trial: (1) receiving another psychological treatment for AjD; (2) meet criteria for another severe mental disorder: alcohol or other substance abuse or dependence, psychotic disorder, dementia, or bipolar disorder; (3) meet criteria for a severe personality disorder or illness; (4) presence of risk of suicide or self-destructive behaviors. Undergoing pharmacological treatment is not an exclusion criterion during the study period, but any increase and/or change in the medication during the study period will imply the participant’s exclusion from subsequent analyses. A decrease in pharmacological treatment is accepted.

The decision about each participant’s inclusion or non-inclusion will be made by the entire clinical team, ensuring a more objective and reliable diagnosis. The telephone interviews will also be recorded, with the patient’s agreement, making independent inter-judge assessment possible.

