#### Waiting list control group

Participants on the waiting list group will be assessed before and after a period of 7 weeks. After completing a post-waiting period assessment, they will be offered the TAO program.

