### Data analyses

The statistical package IBM SPSS Statistics version 22.0 for Windows will be used for data analyses. Baseline differences between groups will be explored for continuous and categorical measures using both t-tests and chi-square tests. Repeated-measures ANOVAs will be used to assess within-group changes over time in primary and secondary outcome measures. Effect sizes will be estimated using Cohen’s d. Linear regression models will be used to study the effect of different variables (e.g., gender, age, and treatment expectations) on adherence and response to the intervention. Any participants who do not complete the post-intervention assessment will be considered drop-outs. On the other hand, the number of times each patient uses the program will be used as the measure of adherence.

Before analyzing the data, a review of state-of-the-art analytic methodology for RCT will be carried out in order to ensure the use of the most suitable statistical analyses. Finally, following SPIRIT and CONSORT guideline recommendations, both intention-to-treat and per-protocol analyses will be reported [34, 36].

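### Participants whose medication is increased or changed after randomisation are excluded from later analyses, with no limit to the per-protocol set, which conflicts with the promised intention-to-treat analysis

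*Protocol article*

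**What the plan says.** The Eligibility criteria section allows medication at entry: "Undergoing pharmacological treatment is not an exclusion criterion during the study period". It then adds a rule about what happens later: "any increase and/or change in the medication during the study period will imply the participant’s exclusion from subsequent analyses". The rule runs one way only: "A decrease in pharmacological treatment is accepted".

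The Data analyses section states that "both intention-to-treat and per-protocol analyses will be reported". It makes no exception for medication changes and does not say which analysis set the rule governs. It defines drop-out by the missing assessment alone: "Any participants who do not complete the post-intervention assessment will be considered drop-outs". A participant who changes medication and completes that assessment is therefore not a drop-out, but is excluded all the same.

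Three other places matter. Randomization and blinding puts allocation after eligibility and consent. The control arm is untreated up to its second assessment: "Participants on the waiting list group will be assessed before and after a period of 7 weeks". The abstract names the endpoints: "BDI-II and BAI will be used as primary outcome measures".

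**The concern.** The rule is listed with the eligibility criteria, but a medication change during the study can happen after allocation. It is then a post-randomisation exclusion. An intention-to-treat analysis keeps participants in the arm to which they were assigned whatever happens later, so the rule and the promise cannot both be carried out as written.

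The exclusion is also plausibly related to outcome. The primary outcomes measure depression and anxiety, and worsening symptoms are one reason why medication might be increased. The arms differ in ways that could affect how often this happens: one receives TAO with weekly calls, the other waits. If the waiting list loses more of its poor outcomes, the benefit of TAO is understated. If the TAO arm loses more, it is overstated. An analyst could also choose between the two readings after seeing the data.

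**Working it through.** **Inputs from the article (Sample size section).** Effect size 0.70, significance level 5% (sidedness not stated), power 80%, 26 per group, dropout about 30%, 34 per group recruited (68 in total). The article gives no rate of medication change, so every exclusion rate below is an assumption.

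**The plan's own figure.** For a two-sample t-test with n per group, the noncentrality is 0.70 × √(n/2). At n = 26 this is 2.524. Power is 80.1% one-sided and 69.7% two-sided, so 26 is reproduced by a one-sided 5% test. The recruited number follows from 26 × 1.3 = 33.8, rounded to 34. That basis is a separate matter; it is noted here only because it sets the starting point for power.

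**Bias with no true effect (outcome SD 1, higher is worse).**

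- *Equal rates, same mechanism.* With 10% or 20% excluded in each arm, the simulated difference is within 0.002 of 0.
- *Moderate link.* Suppose the odds of exclusion are multiplied by e for each SD of worse outcome. Excluding 6.9% of an arm then lowers its mean by 0.064 SD, excluding 15.5% lowers it by 0.137, and excluding about 22% lowers it by 0.190. So 6.9% v 15.5% gives 0.137 − 0.064 = 0.073, and 6.9% v 22% gives 0.190 − 0.064 = 0.126. The range is about 0.07 to 0.13 SD.
- *Extreme case.* If exactly the worst fraction p is removed, the mean shifts by φ(z)/(1 − p), where z is the upper-p normal quantile. For p = 0.15: 0.2332/0.85 = 0.274. For p = 0.05: 0.1031/0.95 = 0.109. The difference is 0.166, or 0.17 SD, which is 0.166/0.70 = 24% of the assumed effect. With a correlation of 0.5 between exclusion tendency and outcome, the same rates give half of this, 0.083.

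**Bias with a true effect of 0.70.** If one severity cut-off triggers the exclusion in both arms, an effective treatment itself makes the rates unequal.

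| Waiting list excluded | Estimate, correlation 0.5 | Estimate, exclusion fully determined by outcome |
|---|---|---|
| 10% | 0.66 | 0.56 |
| 20% | 0.64 | 0.48 |
| 30% | 0.62 | 0.41 |

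**Power.** Dropout of 30% leaves 34 × 0.7 = 23.8 per group. A further 10% loss leaves 34 × 0.7 × 0.9 = 21.4. This product assumes that drop-outs and medication changers do not overlap more than chance.

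| Per group | Noncentrality | Two-sided power | One-sided power |
|---|---|---|---|
| 23.8 | 2.415 | 65.7% | 76.8% |
| 21.4 | 2.291 | 60.9% | 72.8% |

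The medication rule itself costs about 4 to 5 points.

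**The case against.** The strongest reply is that the authors may have meant the rule for the per-protocol set, where such an exclusion is natural, or only for analyses that follow the change. Detailed analysis sets are usually left to an analysis plan that is not shown. The article does cite reporting guidelines for presenting both sets. It is fair that the intent is uncertain. But the article itself states the rule, in unrestricted terms, beside a promise that it does not fit, so this is not an omission to be filled in elsewhere.

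Some stronger readings are tempting but not supported.

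- A reader might infer that the rule removes those who do worst. The article gives no reasons for medication changes, and a change need not follow from worsening. The link to outcome is plausible, not documented.
- A reader might infer that the randomised comparison is bound to be biased. Bias needs rates or reasons that differ by arm, and the article gives no evidence on either.
- A reader might take 61% power as the price of this rule. Dropout alone already brings two-sided power to 66%.

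The exposure is also limited. The waiting list is offered TAO after its second assessment, so the randomised contrast ends there, and later medication changes need not touch it. The rule may also reach only people medicated at entry, a share that the article does not give.

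**Conclusion.** The conflict is real and should be resolved before analysis, because it decides who enters the main comparison in a trial of 68 people. What the documents establish is an unrestricted post-randomisation exclusion that cannot coexist with the promised intention-to-treat analysis. They do not establish that bias will occur, how large it would be, or which arm it would favour.

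Of the sizes above, the moderate-link range of 0.07 to 0.13 SD is the more realistic guide if rates do differ; 0.17 SD assumes perfect selection of the worst outcomes together with a threefold difference in rates. The power loss is secondary, but the sample size makes no allowance for it, since it budgets only for dropout.

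**What to change.** Reconcile the two sections. In Eligibility criteria, confine the medication-change exclusion to the per-protocol or a sensitivity analysis. In Data analyses, state that the intention-to-treat analysis is primary and keeps every randomised participant in the assigned arm regardless of medication change. Record the type and date of each change and report the numbers by arm.

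This takes about two sentences and leaves the recruited number unchanged. The small downside is that the estimated effect then includes any contribution from medication, which the sensitivity analysis would help to show. The change concerns the analysis set only and takes no position on how medication should be managed.
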